## Abstract

**Background:**

The occipito-posterior (OP) fetal head position during the first stage of labour occurs in 10-34% of cephalic presentations. Most will spontaneous rotate in anterior position before delivery, but 5-8% of all births will persist in OP position for the third stage of labour. Previous observations have shown that this can lead to an increase of complications, such as an abnormally long labour, maternal and fetal exhaustion, instrumental delivery, severe perineal tears, and emergency caesarean section. Usual care in the case of diagnosis of OP position is an expectant management. However, maternal postural techniques have been reported to promote the anterior position of the fetal head for delivery. A Cochrane review reported that these maternal positions are well accepted by women and reduce back pain. However, the low sample size of included studies did not allow concluding on their efficacy on delivery outcomes, particularly those related to persistent OP position. Our objective is to evaluate the efficacy of maternal position in the management of OP position during the first stage of labour.

**Methods/design:**

A randomised clinical trial is ongoing in the maternity unit of the Geneva University Hospitals, Geneva, Switzerland. The unit is the largest in Switzerland with 4,000 births/year. The trial will involve 438 women with a fetus in OP position, confirmed by sonography, during the first stage of the labour. The main outcome measure is the position of the fetal head, diagnosed by ultrasound one hour after randomisation.

**Discussion:**

It is important to evaluate the efficacy of maternal position to correct fetal OP position during the first stage of the labour. Although these positions seem to be well accepted by women and appear easy to implement in the delivery room, the sample size of the last randomised clinical trial published in 2005 to evaluate this intervention had insufficient power to demonstrate clear evidence of effectiveness. If the technique demonstrates efficacy, it would reduce the physical and psychological consequences of complications at birth related to persistent OP position.

**Trial registration:**

ClinicalTrials.gov, http://www.clinicaltrials.gov: (no. NCT01291355).

## Background

During the first stage of labour, 10% to 34% of fetuses are in occipito-posterior (OP) position (Figure 1) [1-3]. A cohort study of 1,562 nulliparous women reported an association between epidural analgesia and OP position [4], similar to a retrospective analysis of 30,839 deliveries conducted from 1976 to 2001 [5]. Parity, particularly nulliparity, appears to be also an aetiologic factor [2]. OP position is a malpresentation for delivery. Previous observations have shown an increase of short- and long-term complications, such as an abnormally prolonged labour, maternal and fetal exhaustion, instrumental delivery, emergency caesarean delivery, and severe perineal tears [5-8][9-12]. Similarly, in a prospective cohort study published in 2013, Carseldine et al. reported that OP position early in the second stage of labour is strongly associated with operative delivery: a total of 68% (13/19) women in the occipito-posterior group, and 27% (39/141) in the occipito-anterior group had an operative delivery (unadjusted: P < 0.001). Caesarean section was performed in 37% and 5%, respectively (P < 0.001) [13].

**Figure 1 F1:**
[figure not shown]
**Fetal occipito-posterior (OP) position*.** There are three OP positions: ROP (Right OP), LOP (Left OP), OS (occiput at sacrum). *This image is now in the public domain.

Usual care in the case of diagnosis of OP position is expectant management. Previous studies report that 72-90% of fetuses will spontaneously rotate to an anterior position during the first or second stage of labour [1,3]. Digital rotation of OP to anterior position has been described for the management during the second stage of labour. Although, it has the potential to successfully rotate the fetus and reduce the need for caesarean section, instrumental delivery, and other complications associated with OP position, it may also be traumatic for the fetal head and perineum.

Clinical diagnosis of the OP position is difficult as it is often associated with a deflection of the fetal head, and/or fetal head swelling, and oedema of the maternal cervix [14,15]. Several studies recommend verifying the clinical diagnosis of the fetal head position with ultrasound to increase the diagnosis of OP position early in labour [16,17]. According to Ramphul et al., an abdominal scan is easy to perform and is an accurate and acceptable method of diagnosing the fetal head position in the second stage of labour. It may also be useful in assessment prior to instrumental delivery [18].

### Literature review

A search of Medline and of the Cochrane Library was undertaken for relevant systematic reviews, meta-analyses, randomised controlled trials, and other clinical studies. A Cochrane review on the hands and knees’ posture in late pregnancy or labour for fetal malposition (lateral or posterior) concluded that the adoption of this posture 10 min daily in late pregnancy has the short-term potential to change the fetal position and reduce lumbar pain, but does not influence delivery outcomes [11]. The last randomised controlled trial on this topic was conducted by Stremler et al. in 2005 [19]. Similarly, the results reported a decrease of back pain associated with the hands and knees posture during the first stage of the labour, but the sample size of the study had insufficient power to demonstrate clear evidence to rotate OP in anterior position. The World Health Organisation encourages walking and changing of maternal position to promote spontaneous rotation of the fetal head in anterior position during the labour [20].

The book by [name] described hands and knee positions to facilitate the rotation of the fetal head in anterior mode [21] (Figure 2). According to the author, these positions (resting on the knees, chest leaning forward and back stretched) would provoke fetal head OP rotation to anterior almost immediately. This technique seems simple to implement and acceptable to women according to previous studies that evaluated the experience of similar positions [11,22]. A relative disadvantage of this technique is the organisation of equipment for the mother (infusion, epidural, electronic blood pressure) and fetus (heart monitoring). Regarding the possible effect of the hands and knees’ position on the epidural anaesthesia, a French study conducted by anaesthetists showed that hyperflexion at the hips did not influence the expected epidural analgesia levels [23].

**Figure 2 F2:**
[figure not shown]
**Six fitted hands and knees’ positions*.** *Consent to publish these images was obtained by [name] [name], author of the original book [21].

### Results of a pilot survey at the maternity of the Geneva University Hospitals

Epidemiological data on OP during labour are rare. Prior to starting the study and to elaborate the protocol, we conducted a retrospective analysis of 100 medical records randomly selected among all women who delivered during March 2010, to investigate the prevalence of OP position during labour and delivery, and mode of delivery. The data on the variety of presentation were absent for 25/100 medical records; 19/75 (25%) fetuses were diagnosed in OP position during the first stage of labour; and 9/75 (12%) had a persistent OP position for the second stage of the labour; of the latter, 7/9 were born by caesarean section. These results are more pessimistic than data reported in the literature. However, fetal outcome with OP is still poorly known and the contribution of this position to dystocia may be underestimated.

### Aims

The aim of our study is to evaluate the efficacy of hands and knees’ positions to correct fetal head position in OP during the first stage of the labour.

## Methods/design

We designed a randomised clinical trial, as it is the best study design to evaluate the effects of an intervention. We will compare the hands and knees’ positions (intervention) with expectant management (no intervention). “Expectant” is the standard care in our maternity in the case of OP diagnosis during the first stage of labour. There is no possibility of blinding, either the participant or the attending midwife or obstetrician, given the nature of the intervention. To introduce a “sham position” in the control group may be very difficult to imagine and interpreting the results would be cumbersome (is the proposed position beneficial or the control “sham” position increasing the risk or persistent OP?).

### Recruitment and intervention

Recruitment of women to the study will take place in the delivery room. During the period of recruitment study, we will perform systematically a transabdominal ultrasound to diagnose the fetal head position for each woman during the first stage of labour, to allow a reliable and early diagnosis of OP position.

#### Assessment of eligibility

Research midwives will verify eligibility for the study of all women presenting a fetus in OP position.

#### Inclusion criteria

The study will be limited to nulliparous and multiparous women during the first stage of labour with a cervical dilatation between 2 to 9 cm, a singleton pregnancy at term (≥ 37 weeks’ gestation), and an OP position diagnosed by ultrasound.

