#### Baseline

After consenting to participate in the study and prior to randomisation, women will be asked to complete a questionnaire including: sociodemographic data; resting position spontaneously adopted in late pregnancy; location of the pain perceived during uterine contractions (i.e., lower abdomen, back, other); perceived pain measured by the visual analogue scale (VAS) [18]; the comfort level of their position using a Likert scale (very comfortable, comfortable, neither comfortable nor uncomfortable, uncomfortable, very uncomfortable).

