#### Randomisation

When women give their written consent to participate, a research midwife or the attending midwife will proceed with randomisation through a web-based system provided by the informatics department of the Geneva University Hospitals. Randomisation will be performed using randomly permuted blocks of varying size (4, 6 and 8), stratified by parity (nulliparous/multiparous) and epidural analgesia (yes/no). The ratio for hands and knees versus expectant management is 1:1. After confirming eligibility and consent, the system will return the allocation of the women to the midwife.

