### Statistical analysis

Data analysis and reporting will be performed according to CONSORT guidelines for randomised controlled trials. A descriptive table of baselines characteristics will be reported for participants for both groups. Primary and secondary outcomes will be analysed on intention-to-treat basis. Sub-group analysis and eventually adjustment for the variables used for stratification (parity and epidural analgesia) will be performed. Means and their standard deviations will be calculated for continuous variables, and the statistical significance of differences between groups will be tested using Student’s *t*-test. Proportions will be compared between groups and differences will be tested using the chi-square test. If the distribution of the variables is not Gaussian, we shall use non-parametric statistical tests. The effect of the intervention will be estimated by the relative risk and its 95% confidence interval and p values to test the significance of the differences will be calculated.

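### Adjustment is planned for parity and epidural analgesia only; with entry allowed at 2 to 9 cm, adding cervical dilatation as a pre-specified covariate would bring a small gain in precision

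*Protocol article*

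**What the plan says.** All places are in the protocol article.

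- **Inclusion criteria:** women may enter at "a cervical dilatation between 2 to 9 cm", which is nearly the whole first stage.
- **Randomisation:** allocation is in permuted blocks, "stratified by parity (nulliparous/multiparous) and epidural analgesia (yes/no"). Dilatation is not a stratification factor.
- **Statistical analysis:** for binary outcomes, "Proportions will be compared between groups and differences will be tested using the chi-square test". For the effect measure, "The effect of the intervention will be estimated by the relative risk and its 95% confidence interval". On covariates, "Sub-group analysis and eventually adjustment for the variables used for stratification (parity and epidural analgesia) will be performed".
- **Baseline:** "women will be asked to complete a questionnaire including: sociodemographic data; resting position spontaneously adopted in late pregnancy". The list goes on to pain and comfort. Dilatation is not among the items, although its value must be known to confirm eligibility.
- **Outcome measures:** the primary outcome is an anterior head position at one hour, or at delivery if that comes sooner.

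**The concern.** A woman entering at 2 cm and a woman entering at 9 cm spend the same hour in very different phases of labour. The article itself suggests that head position changes as labour advances. The Background cites 72-90% spontaneous rotation over the first and second stages. In the pilot survey, 19 of 75 fetuses were occipito-posterior in the first stage and 9 of 75 were still so in the second. The primary outcome can also be read at delivery, before the hour is up, so the length of observation may itself depend on how far labour has progressed.

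If dilatation at entry predicts the one-hour position, a chance difference between arms in dilatation would move the estimate, and an analysis without it would give up some precision. There is also a question of timing. The Methods/design section says that blinding is not possible. If the baseline table showed an imbalance in dilatation, a decision made then to adjust for it would be data-driven. Naming the covariate beforehand removes that choice.

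**Working it through.** **Inputs from the article.** 219 women per arm; 10% versus 20% anterior at one hour; two-sided significance level 0.05; power 80%; 1:1 allocation (Sample size and Randomisation).

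**Assumptions not in the article.** Half the women are in advanced labour at entry; the control rate averages 10% over the two halves; the relative risk is 2 in both halves. The gradient between early and advanced labour is varied.

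**Step 1: reproduce the planned size.**
- Without continuity correction: n = [1.96·√(2·0.15·0.85) + 0.842·√(0.10·0.90 + 0.20·0.80)]² / 0.10² = 199 per arm, 398 in total.
- With continuity correction: n′ = (n/4)·[1 + √(1 + 4/(n·0.10))]² = 219 per arm, 438 in total. This matches the article exactly.
- Power of the uncorrected test at 219 per arm is 83.7%.

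**Step 2: chance imbalance in dilatation.**
- SD of the between-arm difference in the share in advanced labour = √(2·0.25/219) = 0.0478, or 4.8 points.
- 1.96 SD = 9.4 points.

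**Step 3: effect on the risk difference.** Shift = 0.0937 × (rate in advanced labour − rate in early labour).

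| Control rates, early / advanced | Shift at 1.96 SD | Share of 10-point target |
|---|---|---|
| 8% / 12% | 0.4 points | 4% |
| 5% / 15% | 0.9 points | 9% |
| 2% / 18% | 1.5 points | 15% |

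These shifts use the control-arm gradient, so they describe the case of no treatment effect. With a relative risk of 2 the gradient in the intervention arm doubles. If the imbalance is split evenly between arms, each shift is then multiplied by (1 + 2)/2 = 1.5.

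**Step 4: power and type I error.** 40,000 simulated trials per scenario, 219 per arm, comparing the uncorrected chi-square test with a Cochran-Mantel-Haenszel test stratified by early or advanced dilatation.

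| Control rates, early / advanced | Power, unadjusted | Power, stratified by dilatation |
|---|---|---|
| 10% / 10% | 84.3% | 84.1% |
| 8% / 12% | 84.5% | 84.6% |
| 5% / 15% | 84.5% | 85.7% |
| 3% / 17% | 84.4% | 87.3% |
| 2% / 18% | 84.6% | 88.3% |

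Type I error was 4.9% to 5.0% for both tests in every scenario. The comparison is with no adjustment at all. If dilatation is associated with parity or epidural use, the planned adjustment may already capture part of the gain.

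**The case against.** The case for leaving the plan alone is substantial.

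- **Design and analysis already agree.** The two stratification factors are the two adjustment variables. The article does not say that no other covariate may be used, and a fuller list could sit in an analysis plan that is not shown. This stands in part: the article does not rule dilatation out. But it is not silent on covariates either. It names a set, and dilatation is not in it.
- **Validity is not in question.** A reader might infer that the comparison is biased or unprotected because dilatation is neither balanced nor modelled. The documents do not support that. Randomisation balances dilatation in expectation, the test and confidence interval already allow for chance imbalance, and the simulated type I error is about 5%. This objection stands in full.
- **The shift is small beside the random error.** At the design rates the standard error of the risk difference is √((0.09 + 0.16)/219) = 3.4 points. A 0.9-point shift is about 0.28 of that and already forms part of it. A 1.96-SD imbalance is also a 1-in-20 event. This stands.
- **The prognostic link is not documented.** A reader might take it as established that dilatation predicts rotation within the hour. The article describes rotation over the whole of labour and gives no rate by dilatation at entry. The link is plausible but unquantified.
- **Recording is inferred.** A reader might also assume that a value in centimetres is already in the data. Eligibility requires dilatation to be known, but the article does not say that it is captured as a baseline variable. The fix has to ask for this.

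**Conclusion.** The point holds as a minor improvement. The article ties adjustment to parity and epidural analgesia while admitting women across 2 to 9 cm, and a plausible prognostic variable that must be assessed for eligibility is not among the covariates it names.

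The unadjusted comparison remains valid, and the sample size of 438 is reproduced and unaffected. The loss is limited to precision and exposure to chance imbalance: about 0.4 to 1.5 points on the risk difference at 1.96 SD, and about 0 to 4 points of power. Only a very steep gradient (2% versus 18%) brings the gain near 4 points; at 5% versus 15% it is about 1 point. These sizes rest on an even split between early and advanced labour, a 10% average control rate and, for power, a constant relative risk of 2. The split and the gradients are not in the article.

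The further benefit, which does not depend on those figures, is that the covariate would be chosen before the data are seen in a trial that cannot be blinded.

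**What to change.** Make two small changes before any outcome data are examined.

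1. State that cervical dilatation in centimetres, as assessed for eligibility, is recorded at randomisation and shown in the baseline table.
2. Extend the adjustment sentence in Statistical analysis so that the adjusted relative-risk model for the one-hour outcome includes dilatation (continuous, in cm) together with parity and epidural analgesia.

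The randomisation scheme and the sample size do not change, and no additional examination is implied. The cost is one recorded value per woman and one more model term. If dilatation turns out to be only weakly prognostic, the gain will be close to nil.

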#### Exclusion criteria

Women under 18 years old, or who have a limited understanding of French, or who have attempted hands and knees’ positions previously during the first stage of labour.

#### Baseline

After consenting to participate in the study and prior to randomisation, women will be asked to complete a questionnaire including: sociodemographic data; resting position spontaneously adopted in late pregnancy; location of the pain perceived during uterine contractions (i.e., lower abdomen, back, other); perceived pain measured by the visual analogue scale (VAS) [18]; the comfort level of their position using a Likert scale (very comfortable, comfortable, neither comfortable nor uncomfortable, uncomfortable, very uncomfortable).

#### Randomisation

When women give their written consent to participate, a research midwife or the attending midwife will proceed with randomisation through a web-based system provided by the informatics department of the Geneva University Hospitals. Randomisation will be performed using randomly permuted blocks of varying size (4, 6 and 8), stratified by parity (nulliparous/multiparous) and epidural analgesia (yes/no). The ratio for hands and knees versus expectant management is 1:1. After confirming eligibility and consent, the system will return the allocation of the women to the midwife.

### Study participation

Table 1 summarises the chronology of the study conduct following the inclusion of participants.

**Table 1 T1:** Summary of the chronology of study interventions

**Time 0:**	**Time 1:**	**Time 2:**	**Time 3**
**Diagnosis of occipito-posterior (OP) position of the fetal head**	**Randomisation and intervention**	**Evaluation of pain and comfort position 15 minutes after randomisation**	**Diagnosis of the fetal head position 1 hour after randomisation**
Action:	Action:	Action for both groups:	Action for both groups:
Confirmation of diagnosis by ultrasound (US).	“Control group” = expectative attitude for 1 hour in a comfortable position, excluding the 6 fitted hands and knees positions.	Women complete a short questionnaire about perceived pain (Visual Analogue Scale) and positional comfort (Likert scale).	Diagnosis of fetal head position by US.
			After the measure of the main outcome, the woman can freely take the position of her choice, including hands and knees.
Information and consent of the woman to participate to the study.			
	“Intervention group” = installation in one of the 6 fitted hands and knees’ position chosen by the woman for at least 10 minutes.		

### Interventions

#### Hands and knees position arm

Immediately after randomisation, women allocated in this group will be invited to choose one of the six positions described by [name] (Figure 2). According to this author, all these positions have the same impact on the OP position. The research midwife will present photographs of the six fitted positions (Figure 2) to help the women deciding which position is the best for her. These positions have three important points to be observed: 1) resting on the knees and, if necessary, on the hands; 2) the abdomen must be thrust forward; 3) the back is always stretched. A pillow should be placed between the legs of the woman in labour to limit discomfort. The woman decides if she wants to place her abdomen on a cushion or leave it unsupported. To help the women to take the appropriate position and to be sure that the position is correct, [name] has trained all midwives working in the delivery room of the maternity in the management of the OP position by specific positions of hands and knees. We shall recommend that participants to keep the position as long as they feel comfortable, but a minimum of 10 minutes is required. After this time, they can remain in the hands and knees’ position or change position if they prefer. Time spent in the evaluated position will be recorded in the data collection form.

#### Expectant management arm

Women allocated in this group will have the usual care in this obstetrical situation. Immediately after randomisation, they will stay in their position, other than the hands and knees’ position. After one hour and following ultrasound verification of the fetal head position, they will be given the option to adopt a hands and knees’ position, if they wish to do so. The position of the woman (standing, sitting, semi-sitting, lying on the back or the side) during this hour will be reported in the data collection form.

